#### 2.5.8. Intervention Fidelity

To enhance fidelity to SDT-based mechanisms, PsicoFIT incorporates prior coach training grounded in SDT principles, the use of structured psychoeducational materials, and a consistent thematic progression across modules and modes of implementation.

#### 2.5.9. Intervention Adherence

In the face-to-face modality, attendance at sessions will be recorded; to support adherence, reminders and weekly reinforcement messages will be sent to the participants. In the semi face-to-face modality, the participants will report the viewing of the capsules; to encourage adherence, the capsules will be sent with encouraging messages, reinforced with a reminder message, and the participants will submit a screenshot as evidence of capsule viewing.

Only those participants who will have completed both the baseline and post-intervention assessments will be included in the dataset, ensuring that the data reflect actual participation in the program.

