**Hypothesis** **3a1.**
*Basic psychological need satisfaction and autonomous motivation will mediate the relationship between the coach’s controlling interpersonal style and healthy lifestyle in both the face-to-face and semi face-to-face modalities, at baseline and post-intervention.*

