**Hypothesis** **3b2.**
*Autonomous motivation will mediate the relationship between basic psychological need satisfaction and burnout in both the face-to-face and semi face-to-face modalities, at baseline and post-intervention.*

Specific Objective 4. To evaluate the moderating effects of the type of participation (face-to-face and semi face-to-face) both at baseline and after the intervention as follows: (a) the relationship between the coach’s controlling interpersonal style and basic psychological need satisfaction (moderating effect 1); (b) the relationship between basic psychological need satisfaction and autonomous motivation (moderating effect 2); (c) the relationship between autonomous motivation and healthy lifestyle (moderating effect 3); and (d) the relationship between autonomous motivation and burnout (moderating effect 4).

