#### 2.2.5. Participant Retention

Strategies to promote retention in the study will include informational and engagement approaches. An induction session will be conducted to explain the details of the intervention and the schedule of activities, with the aim of reminding the participants of the expected benefits, the importance of their participation, and helping them organize their availability for the program.

Additionally, social incentives linked to Club Tigres will be offered, such as visits to training sessions, match tickets, or interactions with club players.

Participants who accumulate consecutive absences or fail to report viewing the video capsules, whichever the case, will be offered support to continue.

In the case of voluntary withdrawal, the participants will be given the possibility to rejoin the study if feasible; otherwise, they will be considered for future editions of the program.

If a participant leaves the study, their contact information and completed evaluations will be recorded. When possible, they will be asked to complete a survey regarding their experience and reasons for leaving.

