### 2.6. Data Analysis

#### 2.6.1. Quantitative Analysis

Due to the practical limitations in following up with those participants who do not complete the program, the primary analysis will be conducted using a per-protocol approach [111], considering only those participants with complete data at baseline and at the end of the intervention; missing data will not be imputed.

This approach will allow for evaluating the changes associated with each intervention under real-world implementation conditions, acknowledging the anticipated risk of participant attrition and that the benefits of randomization may not be fully preserved, while reflecting its applicability in a pragmatic context.

All statistical analyses will consider a 95% confidence level (5% error), ensuring transparency and reproducibility.

Preliminary Analysis. Descriptive statistics for central tendency (mean, median), dispersion (standard deviation and variance), and distribution (skewness and kurtosis) will be estimated for each observed variable. Next, normality tests will be conducted, and the reliability of the instruments will be estimated by measuring their internal consistency through Cronbach’s alpha (α) and McDonald’s omega (ω) coefficients. Subsequently, bivariate correlation analyses will be performed to measure the strength and direction of the relationship between the variables.

Associations among motivational and outcome variables. To examine the associations between the coach’s controlling interpersonal style, basic psychological need satisfaction, autonomous motivation, healthy lifestyle, and burnout, hierarchical multiple regression analyses will be conducted. Separate models will be estimated for each intervention modality (face-to-face and semi face-to-face) and for each measurement occasion (baseline and post-intervention), with predictor variables entered in a theoretically driven manner [42]. Effect sizes and confidence intervals will be calculated to complement the statistical significance, and statistical power will be considered when interpreting the results [112].

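### The both-occasions dataset rule also governs the Time 1 models, so usable Time 1 records of people who leave between week 2 and week 13 are excluded

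*Protocol article*

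**What the plan says.** **The dataset rule.** Section 2.5.9 (Intervention Adherence): "Only those participants who will have completed both the baseline and post-intervention assessments will be included in the dataset". Its stated purpose is that the data should reflect actual participation. Section 2.6.1 says that "the primary analysis will be conducted using a per-protocol approach", "considering only those participants with complete data at baseline and at the end of the intervention; missing data will not be imputed", and gives the difficulty of following up non-completers as the reason.

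**The Time 1 models.** Section 2.6.1 plans hierarchical regressions separately by modality and "for each measurement occasion (baseline and post-intervention), with predictor variables entered in a theoretically driven manner". Hypothesis 1 is stated for both occasions. The mediation hypotheses are stated "in both the face-to-face and semi face-to-face modalities, at baseline and post-intervention". Specific Objective 4 is "To evaluate the moderating effects of the type of participation (face-to-face and semi face-to-face) both at baseline and after the intervention". Section 2.6.1 labels mediation and moderation exploratory. It does not give that label to the Objective 1 associations.

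**The records of leavers.** Section 2.2.5 (Participant Retention): "If a participant leaves the study, their contact information and completed evaluations will be recorded".

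**Timing.** Under 2.3.3 the lifestyle survey is taken at week 0. The coach-style, needs, motivation and burnout scales are taken at week 2, and all instruments are repeated at week 13.

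No section of the article names a separate analysis set for the Time 1 models.

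**The concern.** A cross-sectional model of Time 1 scores needs Time 1 scores only. Neither reason given for the rule carries over to it. Follow-up difficulty is irrelevant to a questionnaire already completed at week 2. Participation is not in question either, because 2.3.3 places most Time 1 scales at week 2 precisely so that respondents have already met the program.

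Two things could be at stake. One is precision, in cells of at most 40. The other is selection: a baseline relationship would be estimated only in people who later reach week 13. The Introduction says autonomous motivation supports behavioural persistence, so completion may be related to a variable in these models. Whether that biases anything depends on what else drives completion.

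This is separate from the comparison of change between modalities, which does need week 13 data.

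**Working it through.** **Plan's own figure.** 2 modalities × 40 = 4 cells × 20 = 80, as stated in 2.2.4. The size was set by feasibility, with no effect size, power or dropout rate, so there is no power calculation to reproduce.

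**Inputs from the article.** 40 per modality (2.2.4), association models fitted by modality (2.6.1), and 5% error (2.6.1, taken as two-sided).

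**Assumed inputs.** A true correlation of size 0.40, and attrition after week 2 of 10% to 40%. The article expects attrition but gives no rate.

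**Step 1: precision, dropout unrelated to the variables.** Power = Φ(atanh(r) × √(n − 3) − 1.96), with atanh(0.40) = 0.4236. The smallest correlation detectable with 80% power is tanh((1.96 + 0.842) / √(n − 3)).

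| Attrition after week 2 | n per modality | 0.4236 × √(n − 3) | Power for r = 0.40 | Detectable r, 80% power |
|---|---|---|---|---|
| 0% (all Time 1 records) | 40 | 2.577 | 0.73 | 0.43 |
| 10% | 36 | 2.434 | 0.68 | 0.45 |
| 20% | 32 | 2.281 | 0.63 | 0.48 |
| 25% | 30 | 2.201 | 0.60 | 0.49 |
| 30% | 28 | 2.118 | 0.56 | 0.51 |
| 40% | 24 | 1.941 | 0.49 | 0.55 |

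Simulation gives 0.74 rather than 0.73 for all 40 records, and 0.60 at 25% random attrition. The formula is adequate here.

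**Step 2: which records can be recovered.** Someone lost before week 2 has no motivation, needs, coach-style or burnout score under either rule, so the table applies only to losses after week 2. As an illustration, suppose 10 of 40 leave and 5 of them go before week 2. The comparison is then n = 35 against n = 30. Power is Φ(0.4236 × √32 − 1.96) = Φ(0.437) = 0.67 against 0.60, about half the gap.

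**Step 3: selection.** The true motivation–burnout correlation is set at -0.40, dropout averages 25%, and n is 40 before dropout.

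| Assumed dropout mechanism | r in completers | Power in completers |
|---|---|---|
| Random | -0.40 | 0.60 |
| Odds halve per SD of motivation | about -0.39 | 0.58 |
| Odds also double per SD of burnout | about -0.33 | 0.43 |

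In the second row the slope of burnout on motivation stays at about -0.40, because selection on a predictor alone does not bias a regression slope. In the third row selection acts on both sides and the association shrinks. A wider run let completion depend on both variables with log-odds of 0.5 to 1.0 per SD. The size of r was then 0.38 to 0.34 at 10% dropout and 0.34 to 0.25 at 40%.

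The slope result in the second row is specific to models with motivation as the predictor. In the needs-to-motivation step motivation is the outcome, so the same protection cannot be assumed there. No size is put on that here.

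**The case against.** The strongest reply is that the restriction is deliberate and disclosed. Section 2.6.1 acknowledges attrition, the Discussion lists attrition bias as a limitation, and 2.2.3 treats failure to complete the instruments as a withdrawal criterion. The primary outcomes are change scores (2.7.1), which need both occasions. Using the same people at Time 1 and Time 2 makes the two sets of models comparable. Mediation and moderation are exploratory, and 2.6.1 says power will be considered when interpreting results.

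Most of this is fair, and it limits the weight of the point. It does not remove it. The disclosure is general and not tied to the baseline models. For change scores the loss is partly unavoidable, whereas for Time 1 models the rule itself creates it. Comparability is kept by showing the completers' results as well. It could also be said that 2.6.1 attaches the per-protocol label only to the primary analysis. But 2.5.9 speaks of the dataset, and if something narrower was meant the text should say so.

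Three stronger readings are tempting and are not supported:

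- **That the baseline associations will be attenuated.** The Introduction links motivation to persistence and low autonomous motivation to later burnout. It does not say that burnout drives dropout. Reasons for stopping given in 2.5.11, such as lack of time, illness or injury, need not track either variable.
- **That the hypotheses are about all enrolled participants at baseline.** They name the modalities and the occasions, and no enrolled population.
- **That a power loss in a pooled sample of 80 describes the association models.** Those are fitted within modality, and the pooled moderation models test an interaction.

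**Conclusion.** The point holds as a modest one. As written, the plan leaves usable Time 1 records out of models that need nothing from week 13. Any such exclusion costs precision: for r = 0.40 in a modality of 40, power of about 0.74 with all records falls to about 0.60 at 25% attrition after week 2, and to 0.68 down to 0.49 over 10% to 40%. These figures rest on an assumed correlation and attrition rate, and on everyone having a week 2 record. Losses before week 2 make the recoverable part smaller.

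Bias is possible but not established. It is essentially absent for the motivation-to-burnout slope if completion depends on motivation only. It reaches about -0.33 in place of -0.40 under the stated assumption that burnout drives dropout too. A reader might infer that the baseline results must be distorted, but the document gives neither the rate nor the mechanism needed to say so.

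The models most affected are the Objective 1 associations at Time 1, which carry no exploratory label. The comparison of change is untouched by this point.

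**What to change.** In 2.5.9 and 2.6.1, limit the requirement for both assessments to analyses of change. Add a sentence such as: *All Time 1 models, descriptive statistics and reliability coefficients use every randomised participant with the relevant Time 1 questionnaires, whether or not week 13 was completed. The same results in participants with both assessments are shown as a sensitivity check.* Make clear in 2.2.3 that the withdrawal criterion on incomplete instruments does not remove completed Time 1 records from these analyses. Report how many people left before week 2 and how many between week 2 and week 13.

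The cost is wording and one extra set of results, since 2.2.5 already keeps the data. The downside is that Time 1 and Time 2 models will have different n. The completers' version alongside allows the two occasions to be compared in the same people.

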#### 2.5.10. Concomitant Care

Restrictions will be established regarding participation in other wellness programs that include psychological, nutritional, or physical activity interventions.

Continuation of any recreational physical activity already practiced by the participants before the study will be allowed, as well as the use of prescribed medications that do not affect variables such as motivation, well-being, or physical activity.

The participants may engage in psychological therapy as long as it does not specifically address motivation for physical activity or psychological well-being using approaches similar to the intervention.

If non-compliance compromising data validity is detected, it will be evaluated whether the participant should be excluded from the final analysis.

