## 2. Materials and Methods

### 2.1. Design

A mixed-methods convergent parallel approach will be adopted [40] within the framework of a longitudinal comparative pragmatic clinical trial [41]. To examine changes and to compare delivery modalities, the participants will be randomly assigned to receive the intervention in either a face-to-face or semi face-to-face modality, with measurements at time 1 (baseline) and time 2 (post-intervention).

Quantitative analyses will include hierarchical multiple regression analyses, pre-post comparisons, and regression-based mediation and moderation analyses [42,43]. Additionally, the acceptability and perceived contribution of the intervention will be explored using a qualitative phenomenological approach [44] through a post-intervention focus group. The findings from the statistical analysis and the results of the phenomenological analysis will be integrated, allowing for a more precise understanding of the intervention’s evaluation, its perceived impact, and the acceptability of each modality.

Although this study does not constitute a controlled trial and does not include a no-intervention control group, to ensure methodological rigor and scientific transparency, it has been designed in accordance with the standard items of the SPIRIT 2013 Statement for clinical trial protocols [45] (see Supplementary Materials S1) and takes as a reference the elements of the Trials Registration Data Set (TRDS) [46] considered by the World Health Organization (WHO). In addition, the description of the intervention has been guided by the Template for Intervention Description and Replication (TIDieR) checklist [47] (see Supplementary Materials S2), with the aim of providing a comprehensive, transparent, and replicable account of the intervention components, delivery procedures, materials, and implementation context.

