#### 2.2.4. Sample Size and Randomization

The study will employ a non-probabilistic convenience sampling [44], including participants who meet the established inclusion criteria and are available during the recruitment period.

The sample size (*n* = 80) was determined pragmatically and based on operational feasibility, considering the resources and organizational requirements of the intervention, including the facilitators’ capacity, the availability of staff responsible for implementation, the total program duration, and the estimated recruitment period.

The participants will be distributed equally between the two intervention modalities, with 40 participants per modality (20 men and 20 women in each; see Table 1).

Randomization will be conducted using a computer-generated procedure, applying stratification to ensure an equitable distribution between the groups. The randomization will be generated and safeguarded by a researcher independent of the intervention. Once the assignment is generated, each participant will be notified individually.

Blinding of the participants and facilitators is not feasible due to the nature of the intervention delivery format. The face-to-face and semi face-to-face modalities differ in observable aspects, such as the type of interaction, communication channels, and module dynamics, making it impossible to conceal the assigned modality. Nevertheless, participants will not receive information regarding the activities or specific structure of the alternative modality. Likewise, facilitators will necessarily be aware of the format of the modality they deliver.

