#### 2.4.2. Football Fitness Training

The face-to-face modality includes, on a weekly basis, one hour of recreational training, two two-hour football-based exercise sessions, and 40 min of autonomous recreational physical activity.

The semi face-to-face modality also includes one hour of recreational training (face-to-face), two sessions averaging 24 min of high-intensity interval training (HIIT) through videos hosted through a digital platform, and 40 min of autonomous recreational physical activity per week.

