#### 2.6.4. Data Monitoring

The study will be overseen by the research team, which will verify protocol compliance, data confidentiality, and information safeguarding. Periodic internal meetings will be held to review progress, safety, and protocol adherence.

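### The concomitant-care section allows randomised participants with complete data to be dropped case by case, with no criterion, timing or masking fixed, so the 5% error of the modality comparison is no longer assured

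*Protocol article*

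**What the plan says.** Section 2.5.10 of the protocol article sets limits on outside care: "Restrictions will be established regarding participation in other wellness programs that include psychological, nutritional, or physical activity interventions". Psychological therapy is allowed "as long as it does not specifically address motivation for physical activity or psychological well-being using approaches similar to the intervention". The section closes with the rule at issue: "If non-compliance compromising data validity is detected, it will be evaluated whether the participant should be excluded from the final analysis".

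The analysis set is defined elsewhere. Section 2.5.9 (Intervention Adherence) admits to the dataset only those who completed both assessments. Section 2.6.1 (Quantitative Analysis) calls the primary analysis per-protocol, defines it by complete data at the two times, and rules out imputation. Neither section makes concomitant care a condition.

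The comparison exposed is a randomised one. Section 2.1 states that "the participants will be randomly assigned to receive the intervention in either a face-to-face or semi face-to-face modality", and Section 2.2.4 adds: "The participants will be distributed equally between the two intervention modalities, with 40 participants per modality". On masking, Section 2.2.4 says: "Blinding of the participants and facilitators is not feasible due to the nature of the intervention delivery format". On oversight, Section 2.6.4 says: "The study will be overseen by the research team, which will verify protocol compliance".

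**The concern.** Two participants in the same modality, both with complete data and both with the same outside therapy, could be treated differently. One could stay in the final analysis and the other be removed, and nothing in the article would show that either decision was wrong. The decision comes after randomisation and turns partly on judgement: whether a therapy resembles the intervention, and whether data validity was compromised. The article does not require it to be made before the week-13 scores are known, or by someone unaware of the modality.

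What is at stake is the between-modality difference in change in the two primary outcomes, healthy lifestyle and burnout. If removal is related to outcome or arm, that difference can shift in either direction. The rule also sits poorly with the aim in Section 2.6.1 of judging change as it occurs in ordinary practice, where some outside care is to be expected.

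**Working it through.** The plan gives no power, effect size, SD or breach rate, so there is no figure of its own to reproduce.

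**1. The sections side by side.** Take a randomised participant with full data at both times and a detected breach.
- Sections 2.5.9 and 2.6.1: in the analysis.
- Section 2.5.10: in or out, after an evaluation.

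The second rule is therefore an exclusion that the stated analysis set does not contain. It is separate from the loss of participants through missing data.

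**2. What is fixed about the evaluation.**
- Trigger: non-compliance that is detected and compromises data validity. The second condition is not defined.
- Decision-maker: not named. Compliance checking lies with the research team (Section 2.6.4).
- Timing relative to outcomes: not stated.
- Masking: none described. Section 2.2.4 rules it out for participants and facilitators.

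**3. In-person contact per week** (Sections 2.4.2, 2.4.3 and 2.5).
- Face-to-face: 1 h + 2 × 2 h training + 0.5 h nutrition + 0.5 h PsicoFIT = 6 h.
- Semi face-to-face: 1 h training. The exercise sessions ("two sessions averaging 24 min of high-intensity interval training (HIIT) through videos"), nutrition and PsicoFIT come by video.

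The rule acts on what is detected, and the article describes no common way of asking. Unequal detection is thus possible, but it is not established.

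**4. Effect on the false-positive rate (simulation).** Assumptions: 40 per arm, standard normal change scores, no true difference, t-test on change at 5% (two-sided assumed), breaches unrelated to outcome.

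| How exclusion is used | False-positive rate |
|---|---|
| No exclusion | about 5% |
| 1 to 4 dropped in one arm, regardless of outcome | 4.8% to 5.1% (bias about 0) |
| 8 breachers in one arm, the 1 to 4 with the least favourable change dropped | 5.5% to 6.1% (bias 0.04 to 0.08 SD) |
| Adversarial, 1 flagged per arm | about 6% |
| Adversarial, 2 and 2 flagged | 7.3% to 7.6% |
| Adversarial, 4 and 1 flagged | 8.2% to 8.3% |
| Adversarial, 4 and 2 flagged | 8.7% to 8.9% |

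Adversarial means that any subset of the flagged participants may be dropped, and the run counts as a false positive if any subset gives significance. That is 2⁴ = 16 analyses for 2 and 2, and 2⁶ = 64 for 4 and 2. The ranges are across repeat runs. With 4,000 runs the Monte Carlo standard error is about √(0.075 × 0.925 / 4000) = 0.4 percentage points.

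**5. Effect on the estimate.** The standard error of the arm difference is √(2/40) = 0.224 SD. Suppose two participants in one arm are flagged at random and each is dropped only if the change score is below average. Each has probability 0.5 of being below, with mean −0.80 SD when below. The expected amount removed is 2 × 0.5 × 0.80 = 0.80, so the arm mean moves by about 0.80/39 = 0.02 SD. That is roughly one tenth of the standard error. A shift of 0.10 SD would need the two flagged to be the two poorest changers of all 40, which happens by chance once in 40 × 39 / 2 = 780.

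**The case against.** The strongest reply is that the rule is narrow and the likely effect small. Exclusion is only considered, and only when non-compliance has been found and is held to damage data validity. Removing serious violators is the ordinary sense of per-protocol, and Section 2.6.1 already concedes that the protection of randomisation may be partly lost. Who decides, when, and under what masking is often settled in an analysis plan.

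Much of this stands, and it rules out several stronger readings that a reader might infer.
- *That mere suspicion is enough.* The text requires detection and a validity problem.
- *That an unblinded team makes the decision.* No decision-maker is named, and Section 2.2.4 speaks only of participants and facilitators. What can be said is that no masking is described.
- *That breaches will be found more often face-to-face.* Contact hours are only a proxy. Attending football sessions need not reveal outside therapy or medication, and the semi face-to-face modality also reports weekly on its capsules (Section 2.5.9).
- *That the 5% level is broken.* If breaches are unrelated to outcome, unequal detection alone leaves it near 5%. The inflation needs choices driven by results, which the article permits but does not plan.

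The core of the point survives. The article does more than leave a detail open: it states a discretionary exclusion from the final analysis that its own analysis-set definition does not include. The concession in Section 2.6.1 concerns attrition and does not cover removal of people who completed both assessments.

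**Conclusion.** The point holds in a limited form. Section 2.5.10 allows case-by-case exclusion of randomised participants with complete data, with no advance criterion, no timing and no masking described, and it does not agree with Sections 2.5.9 and 2.6.1. The 5% error is therefore no longer assured for the modality comparison.

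The size cannot be derived from the article. About 7.5% to 9% is an adversarial bound that assumes 2 flagged per arm or 4 and 2. Milder selective use gives about 5.5% to 6%, and exclusion unrelated to outcome about 5%. A shift of about 0.02 SD is the more realistic order for two flagged participants. With 40 per arm and self-reported outcomes, the change is worth making because it is cheap and removes the discretion, not because a large bias has been shown.

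**What to change.** Replace the closing sentence of Section 2.5.10, and align Sections 2.5.9 and 2.6.1 with it, along these lines:

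> *All participants with complete data remain in the primary analysis in their allocated modality, whatever concomitant care they used. Use of restricted care is asked with the same items in both modalities at the week-13 session. A sensitivity analysis excludes those who report restricted care. The list is fixed before outcome data are examined, and exclusions are reported by modality with reasons.*

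The concomitant-care restrictions themselves are left as they are.

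The cost is a wording change, two or three items in a questionnaire session already planned, and one extra analysis. The downside is that the primary estimate will include some participants with outside care, which fits a pragmatic comparison. The sensitivity analysis shows whether they matter.
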